#### Describing outcome data

The prevalence of each primary and secondary outcome measure listed above will be described using numerators, denominators and percentage by treatment arm separately at six and 12 months follow up.

### Comparing baseline characteristics between treatment arms

Baseline characteristics will be compared informally between treatment arms[38].

### Other baseline analyses

We may undertake other baseline analyses, and if so these will be described in a separate analysis plan.

### Comparisons between treatment arms

All outcome measures are binary in nature. They will be compared between treatment arms using random effects logistic regression with patient at level one and practice at level two. Odds ratios and 95% confidence intervals will be estimated using two-level random intercepts logistic models, with patients at level one and practices at level two. Models will include randomisation stratum as a fixed effect[39]. Three separate analyses will be undertaken [40-42]:

i) adjusting only for stratum (practice level)

ii) adjusting for stratum (practice level) and for the presence of medication-related problems at baseline (patient level).

iii) adjusting for stratum (practice level), baseline medication-related problems (patient level), and deprivation and training status (practice level).

An intention-to-treat analysis will be used such that practices will be analysed in the arms they were allocated to regardless of whether they received the intervention or not[43,44]. Significance will be assessed based on likelihood ratio tests with a p value of < 0.05 taken as significant. Analyses will be undertaken using Stata version 10[45]. Regression models adjusted for stratum and baseline medication problem rates will yield estimates of the cluster and residual variance components, enabling the ICCs to be calculated [45].

#### Primary outcomes

The proportions of "at risk" patients in each treatment arm with the errors of interest will be compared between treatment arms at six and 12 months after the end of the intervention period in each practice.

The ICC and 95% confidence interval will be estimated for each of the primary outcome measures from the regression models adjusted for stratum and baseline medication errors.

If any practices are lost to follow up, a sensitivity analysis will be undertaken replacing the missing follow up data with the baseline data for that practice[43,44].

It should be noted that some patients (for both primary and secondary outcome measures) will become "at risk" between the time of the baseline data collection and the follow up data collections. For the primary outcome measures this may occur because:

• They have a diagnosis of asthma or peptic ulcer recorded on the computer following the time of the baseline data collection

• They reach the age of 75 years following the time of the baseline data collection

• At time of the baseline data collection, they do not fall within our definition of being prescribed an ACE inhibitor or a loop diuretic long-term, but they do so at the six and/or 12 month follow up data collection points

• They join the practice after the time of baseline data collection and fall within one of the "at risk" groups.

We believe that it is important to include these patients in the analysis because the intervention is aimed not only at correcting hazardous prescribing, but also at introducing systems to prevent future errors. Nevertheless, for the primary outcome measures, sensitivity analysis will be undertaken excluding patients that (for the reasons outlined above) become "at risk" between the baseline data collection and the follow up data collections.

#### Secondary outcome measures

The proportion of "at risk" patients in each treatment arm with the error of interest will be compared between treatment arms at six and 12 months after the end of the intervention period.

We acknowledge the potential for type 1 errors associated with significance testing for multiple end points. We will therefore consider our analyses of secondary outcome measures to be partly exploratory in nature, and partly confirmatory of our findings for the primary outcome measures.

### Model checking

Level two residuals (variation between practices) for each model will be assessed for normality and constant variance by normal plots and plotting residuals against fitted values. The variation between practices will be summarised by treatment arm[46].

### Multiple endpoints

No adjustments will be made for multiple endpoints. Findings will be interpreted with caution in view of the number of statistical tests undertaken.

### Sub-group analyses

Sub-group analyses[38] will be undertaken only for primary outcome measures. The following analyses will be undertaken:

i) assessing whether the effect of the intervention varies by practice size

ii) assessing whether the effect of the intervention varies by practice deprivation

These analyses will be undertaken by incorporating a term for the interaction between treatment arm and the (continuous) covariate of interest into the regression model[38]. Where there is evidence of non-linearity the covariate will be categorised at the median value. Significance will be assessed based on likelihood ratio tests with a p value of < 0.05 taken as significant and p values between 0.05 and 0.1 described as there being "some evidence" for an interaction.

### Missing data

A complete case analysis will be undertaken at six and 12 months. If any practices are lost to follow up we will consider, prior to unblinding those undertaking the analysis to treatment group allocation, a range of approaches for undertaking sensitivity analyses to assess the robustness of the findings with respect to missing data.

### Comparing characteristics of participating and non-participating practices

The following characteristics will be compared between participating and non-participating practices:

i) List size (using t test or Mann Whitney U test dependent on distribution)

ii) Number of GPs (Mann Whitney U test)

iii) % of practice population aged ≥ 75 years (using t test or Mann Whitney U test dependent on distribution)

iv) Training status (using χ^2 ^test)

v) Deprivation using IMD2004 (using t test or Mann Whitney U test dependent on distribution).

#### Economic analysis

We will undertake a two-stage economic analysis:

• A within trial analysis of cost per error avoided;

• A modelling analysis of economic impact of error reduction.

A standard approach to economic analysis will be applied[47].

The principal objective of the within-trial analysis is to identify and value the resource use associated with the interventions used in the trial.

The principal objectives of the modelling analysis are to:

• Identify and value the impact on patients' health status of the interventions;

• Identify and value the resource use associated with reduced prescribing errors in primary care;

• Assess the relative value for money of the interventions.

### Perspective

We propose to undertake the economic analyses from the perspective of the NHS in terms of the direct costs of providing an intervention to reduce prescribing errors in general practice.

### Comparators and key parameters under investigation

The evaluation will compare the pharmacist-led intervention with simple feedback. Figure 1 illustrates the comparators and the probabilistic events that are associated with each strategy.

**Figure 1 F1:**
[figure not shown]
**decision-analytic model of intervention to reduce preventable drug related morbidity arising from prescribing errors in general practice**.

For the purposes of the within trial analysis of cost per error avoided we will examine the differences in costs of the pharmacist-based intervention compared with simple feedback, in the context of error rate reduction.

For the modelling analysis of cost per quality adjusted life year (QALY) gained, we will examine the differences in overall NHS costs, in the context of QALYs gained.

### Sample size for the economic analysis

The study cannot be powered to detect differences in costs because there is no prior study upon which to base a power calculation. From the 72 practices recruited to the trial, just over 1000 patients (who have been identified to be at risk from potentially hazardous prescribing or medicines management) have consented for the research team to access their medical records for the purposes of the economic analysis.

### Outcome measures to be included in the economic analysis

Pilot work on data collection for the economic analysis showed this to be very time consuming and we therefore decided it would not be possible to collect data for all the outcome measures. We will collect data on outcome measures 1, 2, 3, 5, 7 and 8. We have thus decided not to collect data for the economic analysis for outcome measures 6, 9 and 10, partly because of the problems we have had with data ascertainment (as outlined above). In addition, the numbers of patients identified for outcome measure four are too low to allow for meaningful within-trial economic analysis and so this outcome measure will also not be included.

### Time horizon (follow-up period)

Error rates in practices in both groups will be followed up for 12 months following the completion of the intervention in each practice

### Costs

In this cluster trial, costs will be incurred at both the patient and cluster (practice) level. Randomising by cluster can lead to imbalances between treatment arms in practice or patient level factors, including resource use.

#### Costs measured at practice level

The costs measured at practice level will be the costs of setting-up and delivering the intervention.

#### Costs measured at patient level

The costs measured at the patient level will be any costs of delivering the intervention that can be linked to individual patients.

In the modelling analysis, error-related resource use data will be collected from patients who have consented to access to their medical records ("consented numerator"). NHS resource use data will be collected retrospectively for the 12 month period before the intervention (baseline) and for 12 months after the intervention (follow-up) for the consented numerator. This will allow us to adjust our analyses for baseline cost[48].

Variable costs refer to items where the quantity of resources used is determined only by the need for them as inputs to individual patient care. Variable resource use associated with the interventions (time spent, costs of telephone calls, printing and posting) will recorded for each patient. Fixed costs are those costs that are not affected by patient activity in the short term. UK standard costs will be used for unit costs. This may somewhat over- or under-estimate local unit costs, but allows explicit comparison of costs and local adjustments can be made. Unit costs associated with the intervention will be obtained from the Personal Social Services research Unit (PSSRU)[49], Department of Health reference tables and other reference costs.

### Within trial analysis of outcomes

Outcomes used in the within-trial analysis of cost per error avoided will be number of prescribing errors in each treatment arm.

### Modelling analysis of outcomes

Outcomes used in the modelling analysis will be derived from published evidence on the link between error reduction and impact on health. The PINCER study is not designed to calculate the impact of the intervention on patient health outcomes, either in terms of sample size or length of follow-up. Use of proxy measures such as number of primary and secondary care contacts (hospital admissions, accident and emergency visits and outpatient visits) may be subject to difficulties if considered as patient outcomes. This is because the intervention may lead to increased NHS contact in the short term. We will model the long-term benefit associated with avoidance of errors.

Literature review will be used to obtain published utility weights to allow QALY generation and cost utility analysis.

### Within trial analysis of costs

Costs calculated in the within-trial analysis will be cost of intervention for each patient enrolled in the trial for both treatment arms. These data will be presented separately for the two treatment arms. If required, differences in the mean cost between the treatment arms will be estimated using a two level random linear effects model with patient at level one and practice at level two, to take account of the clustered nature of the data. Baseline costs at practice level will be included as covariates in the model. The assumptions for undertaking random effects linear regression will be assessed using residual plots and in addition the robustness of the analysis to non-normality will be assessed by estimating 95% confidence intervals around the difference in mean costs using bias corrected non-parametric bootstrapping. If the assumptions for undertaking random effects linear regression are not met, we will consider aggregating the patient level cost data to the level of the practice. Comparisons between treatment arms at practice level will be made using a two sample t-test on the original dataset, or on a bootstrapped dataset, depending on the normality of the distribution of practice level costs[50].

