### Allocation of trial interventions

The practice was the unit of allocation. Eligible GP practices agreeing to participate in the trial were stratified by centre (two strata: Manchester and Nottingham) and the size of the patient population in each general practice (three strata: <2500, 2500–6000, >6000) and randomly allocated within strata (1:1 ratio) to the two treatment arms.

The reason for stratifying by centre was to help ensure an even distribution of practices allocated to each of the intervention groups within each centre. The reason for stratifying by size of the patient population in each general practice was because a trial of educational outreach suggested that the larger the practice the more difficult it is to make changes[24].

Block randomisation, using non-predictable block sizes of either two or four, was used to ensure a similar number of practices in each arm. Practices were centrally randomised as they were recruited using the independent web-based randomisation service provided by the Clinical Trials Unit (CTU) at the University of Nottingham. Access to the sequence was confined to the CTU Data Manager (who was independent from the study team). The sequence of treatment allocations will remain concealed until all data analyses have been completed.

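### The within-trial cost comparison omits the randomisation strata, so its interval loses precision to the extent that centre and practice size predict cost

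*Protocol article*

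**What the plan says.** **Design.** Under Allocation of trial interventions, practices were "stratified by centre (two strata: Manchester and Nottingham) and the size of the patient population in each general practice", with three list-size bands, and "randomly allocated within strata (1:1 ratio) to the two treatment arms". Allocation used "Block randomisation, using non-predictable block sizes of either two or four". Two centres by three bands make six strata. The Discussion gives 72 practices, 36 per arm.

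**Clinical models.** Under Comparisons between treatment arms: "Models will include randomisation stratum as a fixed effect". That section is written for binary outcomes, so it does not extend to costs.

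**Costs.** Under Within trial analysis of costs, intervention costs are presented by arm. If required, the difference in mean cost is estimated with a two-level linear model, of which the protocol says: "Baseline costs at practice level will be included as covariates in the model". If the model assumptions fail, aggregation to practice level will be considered, and then: "Comparisons between treatment arms at practice level will be made using a two sample t-test on the original dataset, or on a bootstrapped dataset".

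Stratum is not mentioned in any section of the economic analysis. Practice size appears there only as a sensitivity-analysis topic.

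**The concern.** When allocation is balanced on a factor that predicts the outcome, the true sampling variance of the arm difference falls. An analysis that leaves the factor out keeps that variation in its standard error and so reports an interval that is too wide.

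The protocol gives some reason to expect stratum to matter for cost. Set-up and delivery costs arise at practice level and are partly fixed, so the cost per patient may vary with list size. Size of practice is also one of the two named economic sensitivity topics. The Costs section itself warns: "Randomising by cluster can lead to imbalances between treatment arms in practice or patient level factors, including resource use". Stratification dealt with part of that risk at the design stage, but the cost analysis does not use it.

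The cost difference is the numerator of cost per error avoided, the trial's second objective. The protocol also says that the study cannot be powered for costs, so precision already provided by the design is worth keeping.

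**Working it through.** The protocol states no figure for the cost comparison, so there is none to reproduce.

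**Inputs from the protocol:** 36 practices per arm, six strata, 1:1 allocation within stratum.

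**Assumptions:** R2, the share of practice-level cost variance explained by stratum; stratum sizes of 4, 12 and 20 practices per centre; equal cost variance in the two arms, except in step 4.

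**1. Formula for the fallback t-test.** Let S be the within-arm variance of practice-level cost.
- Variance that the t-test estimates: 2S/36.
- True variance under balanced strata: 2S(1 - R2)/36.
- Ratio of interval widths: 1/sqrt(1 - R2).

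**2. Numbers, with a simulation of 72 practices as a check.**

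| R2 (assumed) | 1/sqrt(1-R2) | Simulated width ratio, t-test to stratum-adjusted | Coverage of the t-test's nominal 95% interval |
|---|---|---|---|
| 0 | 1.00 | 1.00 | 95.3% |
| 0.05 | 1.03 | 1.03 | 95.0% |
| 0.10 | 1.05 | 1.06 | 96.0% |
| 0.20 | 1.12 | 1.12 | 96.8% |
| 0.30 | 1.20 | 1.20 | 98.2% |

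The stratum-adjusted interval covered 94% to 95% throughout. A second simulation, with strata of 6, 12 and 18 per centre, gave 1.05 to 1.06 at R2 = 0.10 and 1.20 at R2 = 0.30, so the result depends little on stratum sizes.

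**3. Degrees of freedom.** The t-test has 72 - 2 = 70. Arm plus six stratum means leaves 72 - 7 = 65.

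**4. Unequal variances.** If feedback-arm costs hardly vary (SD 0.1 times that of the pharmacist arm), the t-test interval is still 5% and 20% wider than a fully stratified comparison at R2 of 0.10 and 0.30. A stratum main effect alone then recovers less: ratios of 1.03 and 1.10.

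**5. Bootstrap.** Resampling n practices with replacement gives a variance (n - 1)/n times the usual unbiased estimate. In an arm of 36 split into six cells, weighted by cell size, the factors combine to (36 - 6)/36 = 0.83 whatever the cell sizes. The standard error is then multiplied by sqrt(0.83) = 0.91, about 9% too small. Resampling the whole arm gives 35/36 = 0.97, and sqrt(0.97) = 0.99. In a simulation with 3, 6 and 9 practices per arm per centre and no stratum effect, percentile intervals covered 91.3% with within-cell resampling and 93.2% with unstratified resampling.

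**The case against.** Several points on the other side stand.

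- **The analysis is conditional.** The model is fitted only if required, and aggregation to practice level is only to be considered. A reader might infer that the cost interval simply is too wide. The document does not support that: it depends on a comparison being made and on stratum predicting cost.
- **The figures are for the fallback.** The two-level model with its baseline covariate was not simulated. A reader might infer that this covariate cannot help, because the cost of the intervention has no pre-intervention value and the only baseline costs described are NHS resource use in consented patients, collected for the modelling analysis. But the protocol does not define baseline practice costs, so they may carry some of the information on size and centre.
- **R2 is unknown.** At R2 = 0.50 the interval would be 42% wider, but nothing in the protocol supports a value that high. At 0.10 the loss is small.
- **Little turns on the interval.** The pharmacist arm receives the feedback plus a pharmacist, so the sign of the cost difference is hardly in doubt. Uncertainty in cost per error avoided comes from a separate bootstrap of the ratio.

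Two further objections carry less weight. A cost model need not mirror the clinical models, and an article may leave a full covariate list to an analysis plan. But this section does specify a model, a covariate, a fallback test and a bootstrap, and an unadjusted two-sample t-test cannot take stratum in. The practice-size sensitivity analysis does not restore the lost precision.

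**Conclusion.** The point holds as a loss of efficiency. The cost comparison as specified does not use the randomisation strata, either in the two-level model's named covariate or in the fallback t-test. The fallback interval is wider than the design delivers by a factor of about 1/sqrt(1 - R2): nothing at R2 = 0, about 5% at 0.10 and about 20% at 0.30. These figures rest on an assumed R2, and on similar cost variance in both arms if a stratum main effect is to recover the whole loss. In the two-level model the loss may be smaller, by an amount that cannot be derived from the document.

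A reader might infer a biased cost difference or an inflated type I error. Neither follows, because the error is conservative. The omission is still worth correcting: the strata are recorded, and the protocol states that quantitative analysis had not been undertaken at submission.

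**What to change.** In Within trial analysis of costs:

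1. Add randomisation stratum (centre by list-size band) as a fixed effect in the two-level cost model, alongside baseline cost.
2. Replace the fallback two-sample t-test with a practice-level linear regression of cost on arm and stratum, using a robust standard error if the arm variances differ.
3. For any bootstrap of the cost difference, resample whole practices within arm and re-estimate the stratum-adjusted difference in each resample. Do not resample naively within arm-by-stratum cells unless a small-cell rescaling is applied. With six cells in 36 practices that understates the standard error by about 9%, and would replace a conservative interval with one that is too narrow.

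The cost is a few lines of wording and code and about five of 70 degrees of freedom. No new data are needed.

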### Modelling analysis of costs

The practice level cost of the intervention will be combined with patient-level costs of error management. The cost per patient will be estimated over the study period. The costs for each event (GP surgery visit, investigations, out of hours, accident and emergency, outpatient and hospital admission costs) will be estimated for each patient in the trial for both treatment arms. The costs will be calculated as resource use multiplied by unit cost and will be reported descriptively, both as resource use and cost data, for each error, with means and ranges presented.

These data will be used to populate the modelling economic analysis. Where there are gaps, these data will be supplemented with data from the literature. Distributional forms of secondary data will follow modelling convention. Literature review will be used to validate the primary error-related resource use data and to assess any long term resource use consequences not detected during the study period.

### Incremental cost-effectiveness ratios (ICERs)

Incremental cost effectiveness ratios will be calculated for the trial-based analyses and sensitivity analyses.

The effectiveness measure for the calculation of incremental cost effectiveness ratio will be cost per unit of outcome. For the within-trial analysis we will use errors. If the lower cost intervention is also associated with better outcomes than the more costly comparator, this will be treated as efficient. In this scenario, incremental ratios would not be calculated for this intervention, since its use would lead to both net savings and greater benefits. Incremental cost effectiveness ratios will be calculated if the higher cost intervention is associated with better outcomes. The incremental ratios will be calculated as:

Statistical analysis is not appropriate to test the robustness of ICERs. It is not possible to generate 95% confidence intervals around ICERs because the ratio of two distributions does not necessarily have a finite mean, or therefore, a finite variance[50]. Therefore, generation of a bootstrap estimate of the ICER sampling distribution to identify the magnitude of uncertainty around the ICERs is required. Bootstrapping with replacement will be employed, utilising MS Excel^®^, using a minimum of 1000 iterations to obtain 2.5% and 97.5% percentiles of the ICER distribution.

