#### Pharmacist intervention

Those practices randomly allocated to this arm received simple feedback and in addition, had a complex pharmacist-led IT-based complex intervention.

First, the pharmacist arranged to meet with members of the practice team to discuss the computer-generated feedback on patients with medication errors. All doctors were encouraged to attend this meeting along with at least one member of the nursing staff, the practice manager and at least one member of the reception staff.

Before the meeting, wherever possible, all relevant members of staff were provided with a brief summary of the objectives of the pharmacist-led intervention and a summary of the findings from the computer search.

At the meeting the pharmacists were asked to use the following approach derived from the principles of educational outreach[21] while also taking account of human error theory[6]:

• Establish professional credibility by explaining their own background in clinical pharmacy and their affiliation with either the University of Manchester or University of Nottingham (depending on the site they are working from)

• Take a non-judgemental approach in all discussions with members of the practice team

• Outline the findings from the computer search

• Explore the views of team members about the findings

• Investigate the baseline knowledge of team members regarding the importance of each of the errors

• Provide clear, concise, evidence-based materials on each of the errors, encouraging active participation by team members

• Explore the views of team members on the underlying causes of the medication errors (using root-cause analysis techniques[22] where appropriate)

• Explain their availability to work part-time with the practice over the following 12 weeks to:

- Help take corrective action in individual patients with medication errors

- Help improve the systems operating in the practice in order to prevent future errors.

• Encourage the team to agree on an action plan with clear objectives

• Ask for a member of the practice team to volunteer to liaise with the pharmacist over arrangements for making changes to individual patients' medication and introducing changes to systems within the practice

• Ask the practice to agree to a follow up meeting within four to six weeks of the initial meeting.

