### Cost effectiveness acceptability curves and net benefit

A cost effectiveness acceptability curve will be constructed to express the probability that the cost per extra unit of outcome gained from within the trial (y-axis) is cost effective as a function of the decision-maker's ceiling cost effectiveness ratio (λ) (x-axis)[51]. Net benefit will be determined when λ is £30 000. For the within-trial analysis we will use cost per error avoided.

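### Percentiles of bootstrapped ICERs rank dearer-and-worse replicates as best value, so the interval for cost per error avoided is wrong unless the error reduction is clearly significant

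*Protocol article*

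**What the plan says.** The section on incremental cost-effectiveness ratios warns that "the ratio of two distributions does not necessarily have a finite mean, or therefore, a finite variance", rules out ordinary confidence intervals for that reason, and turns to the bootstrap, "using a minimum of 1000 iterations to obtain 2.5% and 97.5% percentiles of the ICER distribution".

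The same section says when a ratio is formed at all. If the cheaper option is also the better one, "In this scenario, incremental ratios would not be calculated for this intervention, since its use would lead to both net savings and greater benefits". Otherwise, "Incremental cost effectiveness ratios will be calculated if the higher cost intervention is associated with better outcomes". Both sentences concern the trial result. Nothing is said about a single bootstrap replicate in which the pharmacist arm is dearer and has more errors.

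Two other places fix the sign of the cost difference. Under the pharmacist intervention, practices "received simple feedback and in addition, had a complex pharmacist-led IT-based complex intervention". Under the within-trial analysis of costs, "Costs calculated in the within-trial analysis will be cost of intervention for each patient enrolled in the trial for both treatment arms", so downstream savings are not counted.

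The next section adds an acceptability curve "to express the probability that the cost per extra unit of outcome gained from within the trial (y-axis) is cost effective", together with net benefit at a ceiling of £30 000. The effect unit is errors: "For the within-trial analysis we will use cost per error avoided".

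**The concern.** A percentile interval is meaningful only if the sorted values run from best to worst. ICERs do not do so once replicates fall in more than one quadrant of the cost-effectiveness plane. Here two quadrants matter: dearer with fewer errors (positive ratio) and dearer with more errors (negative ratio). The second is the worst possible outcome, yet it sorts below every positive ratio and reads as cost saving, which the cost definition makes essentially impossible.

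Bootstrapping avoids the need for a finite variance, but it does not put the replicates in order of value. If the section's rule on when to calculate a ratio were applied replicate by replicate, the dominated ones would be deleted and the limits would describe only the replicates in which the intervention worked. Neither reading gives a valid interval for the main within-trial economic result.

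**Working it through.** **Inputs from the protocol article.** Sample size section and Table 2: error rates 5.13% v 2.88%, 1.69% v 0.95% and 17.62% v 9.90%; ICCs 0.01082, 0.00657 and 0.00952; cluster sizes 63, 439 and 105; two-sided alpha 0.05; at least 80% power with 34 practices per arm.

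**Assumptions, not in the article.** Incremental cost is positive in every replicate. The bootstrap distribution of errors avoided is normal with mean z in SE units. The point ICER is scaled to 1. In the simulation the SE of the cost difference is 10% of its mean.

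**1. The plan's own figures.** The two-proportion formula (pooled variance, no continuity correction) gives 1191, 3733 and 312 patients per arm. The design effect 1 + (m − 1) × ICC is 1.671, 3.878 and 1.990. Practices per arm are 1191 × 1.671/63 = 31.59, 3733 × 3.878/439 = 32.97 and 312 × 1.990/105 = 5.91. Rounded up and doubled, these give 64, 66 and 12, as in Table 2. With 34 practices per arm the expected z is 2.91, 2.85 and 6.75.

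**2. Share of adverse replicates.** q = Φ(−z). At the three design effects q is 0.18%, 0.22% and about 0. It reaches 2.5% at z = 1.96. Beyond that share the raw 2.5% percentile is a negative ratio.

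**3. Effect on the upper limit.** With cost held fixed, the correctly ordered upper limit is z/(z − 1.96). The raw 97.5% percentile is z/(z + Φ⁻¹(0.025 + q)), because the adverse replicates have been moved to the bottom of the ordering.
- z = 2.8: raw 2.8/(2.8 − 1.918) = 3.17; correct 2.8/0.84 = 3.33; about 5% too low.
- z = 2.24: q = 1.25%; raw 2.24/(2.24 − 1.780) = 4.87; correct 2.24/0.28 = 8.0.

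**4. Simulation, 1,000,000 replicates, cost also varying.**

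| z | Raw percentiles | Adverse ranked worst | Adverse dropped |
|---|---|---|---|
| 4 | 0.63 to 2.00 | 0.63 to 2.00 | 0.63 to 2.00 |
| 3 | 0.57 to 2.85 | 0.58 to 2.91 | 0.58 to 2.85 |
| 2.8 | 0.55 to 3.20 | 0.56 to 3.37 | 0.56 to 3.21 |
| 2.5 | 0.52 to 3.93 | 0.54 to 4.64 | 0.54 to 3.94 |
| 2.24 | 0.47 to 4.90 | 0.51 to 8.1 | 0.51 to 4.94 |
| 1.64 | −5.19 to 8.04 | 0.44 to unbounded | 0.44 to 8.4 |
| 1.0 | −9.2 to 10.18 | 0.33 to unbounded | 0.32 to 12.03 |

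Fieller limits agree with the re-ranked column where they are finite: 0.56 to 3.36 at z = 2.8 and 0.51 to 8.02 at z = 2.24. Dropping adverse replicates leaves the upper limit almost where the raw percentile put it.

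**5. How often it would happen.** Under the article's rule no ICER is calculated when the point estimate shows no error reduction. The affected trials are therefore those with 0 < observed z < 1.96, as a share of all trials: Φ(1.96 − θ) − Φ(−θ), where θ is the true effect in SE units.
- 80% power, θ = 2.8: 0.200 − 0.003 = 0.198.
- Half that effect, θ = 1.4: 0.712 − 0.081 = 0.632.
- No effect, θ = 0: 0.975 − 0.500 = 0.475.
- Table 2 effects, θ = 2.91 and 2.85: 0.169 and 0.185. For renal monitoring (6.75) it is essentially nil.

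**The case against.** Several points on the other side stand.
- At the planned effect the interval is nearly right. Simulated coverage of the raw interval at true z = 2.8 is 97.6%, against 94.9% when correctly ordered, so on average it is conservative. That average does not make a negative lower limit interpretable in the trial that reports one.
- This is a secondary, descriptive interval. The clinical analysis is untouched.
- The acceptability curve and net benefit are already planned and have no ordering problem if built from net benefit.
- The article does not say whether ICERs are formed per outcome or over pooled errors, so applying a single outcome's z is an assumption. Pooling could raise z.

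Three stronger readings might be inferred, and the documents do not support them. First, that nearly every null trial would report a bad interval: the rule on calculating ratios removes trials whose point estimate shows no error reduction, which leaves 47.5%. Second, that the plan would falsely declare cost-effectiveness at some rate: no rule compares the upper percentile with a ceiling, and the percentiles are offered only to show the magnitude of uncertainty. Third, that the plan conceals the chance of dominance: the acceptability curve is a planned display of that uncertainty.

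It can also be said that replicate handling is a detail for a fuller plan. But the article states the percentile rule explicitly, and both ways of carrying it out give wrong limits.

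**Conclusion.** The point holds as an error in a stated analysis rule, limited to the within-trial economic result. The distortion is negligible at z of about 3 or more, about 5% on the upper limit at z = 2.8, and clear at z of about 2.2 to 2.5. Below 1.96 the interval is invalid. About 20% of trials would report such an interval at 80% power, 63% at half that effect and 47.5% under no effect.

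These shares rest on positive incremental cost in every replicate and a normal error difference; they do not depend on the assumed cost SE. The planned curve and net benefit lessen the harm but leave the misleading interval in the report. The curve's wording also allows it to be coded as ICER below the ceiling, which would count dominated replicates as cost effective. The wording permits that coding but does not require it.

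**What to change.** In the ICER section, replace the plain percentiles with the following:
- Rank replicates that are dearer with more errors as least favourable, above every positive ratio, before taking the 2.5% and 97.5% points; or use Fieller limits.
- Report the upper limit as unbounded (dominated) when 2.5% or more of replicates show no error reduction.
- Do not drop replicates by quadrant. Report the proportion in each quadrant of the cost-effectiveness plane.

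The ordering must be stated even when fewer than 2.5% of replicates are adverse. At z = 2.24 only about 1.3% are, yet the raw upper limit is 4.9 rather than about 8.

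In the acceptability-curve section, define the curve as the proportion of replicates with positive net benefit, and give a 95% bootstrap interval for incremental net benefit.

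The cost is a change of wording and a few spreadsheet columns on the same replicates. The article says quantitative analysis had not begun, so the change could be made before results were known. The downside is that no finite upper ICER limit is reported when the effect is unclear.
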